### 2.6.- Interventions

The intervention program will last for 6 weeks with 2 sessions/week for a total of 12 sessions. This general training protocol structure is based on studies from *Mirelman et al*. [15, 38] and *Shulman et al*. [39], and adapted to fit the GVRE and training characteristics. A 2-session per week instead of 3 will be implemented for two reasons: there seems to be no evidence pointing to better results in interventions having 2 or 3 sessions per week, and the dispersion of elderly population in Lleida will make it easier for participants to attend training with a slightly lower frequency [19, 40]. All changes to the original training protocol structure are based on feedback from a feasibility study performed before the RCT with PWPD and physiotherapists [41]. First-hand information was collected regarding difficulties found and improvements that could be made while using the GVRE rehabilitation system. Improvements were made in fixing of issues within the software and adjusting the training duration, frequency and speed increases.

During the sessions, all participants will be secured by a harness with no weight liberation attached to a safety structure to ensure there is no risk of falls. All sessions will be supervised by at least one physiotherapist with experience managing PWPD, neurorehabilitation and tDCS.

Exercise intensity will be monitored based on the heart rate reserve (HRR; the difference between resting heart rate and maximum heart rate) [42]. Perceived exertion will be recorded using the Borg scale [43]. Moderate intensity (60% of HRR or up to 6 on the Borg scale) will not be exceeded in the sessions. In any case where participants exceed safe intensity levels, any block in progress will be stopped and the rest period will start immediately. Any issues will also be communicated to the participants’ neurologist.

#### Group 1: Treadmill + GVRE + tDCS

This group will follow a treadmill gait training protocol that will last for a total of 6 weeks. Each participant will attend 2 sessions every week, for a total of 12 sessions. All sessions will begin with a 3-minute warm up block walking on the treadmill with no GVRE. The duration of sessions will increase as weeks progress, from a starting duration of 20 minutes to a final duration of 45 minutes. The first week will comprise 4 blocks of 5 minutes each. On the second week, one block will be added, for a total of 5 blocks of 5 minutes. Weeks 3 to 6 will also have 5 blocks of increasing duration, from 6 to 9 minutes, respectively. A 3-minute rest will be given after each block on all weeks (Fig 2).

**Fig 2 pone.0307304.g002:**
[figure not shown]
Progression of training duration and tDCS application.

The treadmill speed for the first week will be set at 85% of the normal walking speed achieved at the 10-meter walking test on the ground. The second week will be at 90% of that speed. Weeks 3 to 6 will all have a set speed based on a 5% increase on the previous week’s speed.

Along with the treadmill gait training, a GVRE will be applied to this group by setting a wide screen TV in front of the treadmill. Two HTC SteamVR 2.0 sensors will collect information from two HTC Vive 3.0 Trackers strapped to the participants’ feet. This data will be processed by the computer and represented in the GVRE on the screen [44] (Fig 3).

**Fig 3 pone.0307304.g003:**
[figure not shown]
GVRE + treadmill set-up.

This way, the participant will be able to interact with the virtual environment by altering his walking patterns on the treadmill. The GVRE involves the participant in a “walking your dog” task, allowing the participant to choose among different colors for the dog and naming it. The dog will walk besides the participant for the entirety of every session [23]. The dog animation will change along the training, with a slow walking animation on the first two weeks, a faster walk on the third and fourth, and a light trot on the fifth and sixth weeks, so that all participants experience the feeling of improvement of the dog increasing its speed. The other gamification elements include a progress bar, green/yellow/red indicators depending on performance, difficulty progression, customized leveling up and score systems. Three different virtual environments will be created: park, city and countryside, and the training will be carried out for 2 weeks on each one of them. Level of difficulty in the GVRE will be modified through 5 different mechanisms: speed (as explained previously), obstacles, distractors, visibility, and path width (Fig 4).

**Fig 4 pone.0307304.g004:**
[figure not shown]
Increase of the difficulty through the modification of mentioned variables.

Obstacles will depend on the environment initially set, but will include bricks, traffic cones and other similar items. During the first and second weeks, obstacles will appear every 30 sec., forcing the participant to dodge them by modifying their walking pattern on the treadmill. For weeks 3 and 4 obstacles will appear every 25 sec., and it will be reduced to every 20 sec. on weeks 5 and 6. Whenever the participant gets close enough to an obstacle, the object will light up with an orange circle to encourage a dodging step, and it will turn green or red depending on whether there was a collision or not (Fig 5). This will work as feedback for participants to better calculate distances during the rest of the session.

**Fig 5 pone.0307304.g005:**
[figure not shown]
Gamification feedback on obstacle management.

Distractors will appear on weeks 2, 4 and 6, and will comprise different sounds and visual information to alter the participant’s focus. Examples of this will be crossing animals making sounds, rivers, building sites and people walking by, depending on the environment.

Visibility will be altered in two ways: by changing the environmental light and via the introduction of fog. The first week will be carried out in morning daylight and no fog; the second week will be at noon with no fog; the third week will be in the morning and will have light fog at the latter half of the blocks; the fourth week will be during evening and will have medium fog at the two final blocks; the fifth week will be during evening and will have medium fog at the two final blocks, and the sixth week will be during nighttime and thick fog will be used at the two final blocks (Fig 6).

**Fig 6 pone.0307304.g006:**
[figure not shown]
Difficulty increase based on visibility limitations.

Path width will be altered to challenge the participants to walk in a more saturated environment: weeks 1 to 2 will comprise a 4-meter pathway, which will be reduced to 3 meters in weeks 3 and 4 and down to 2 meters in weeks 5 and 6.

Participants will also be able to go up one level after the first session if they complete 3 blocks with over an 80% success in obstacle management. This will be limited to only one level promotion per week. Visual metrics will be used to reinforce the feeling of reward when successfully finishing blocks. Moreover, leaderboards regarding scores on obstacle management will be shown to participants in order to keep them engaged and motivated throughout the training.

This group will also receive the treadmill gait training protocol on the virtual reality environment with an anodal-tDCS intervention. Each session will begin with the anodal-tDCS setting. This will consist in placing two turned off sponge electrodes with a total surface of 35cm^2^ on the participant’s scalp after applying a saline solution. They will be set in place using straps. The anode will be placed over the left-Dorsolateral Prefrontal Cortex (DLPFC), identified as the F3 position based on the 10–20 International EEG System, and the cathode will be placed over the right DLPFC [30, 31]. After the 3-minute warm-up block, the anodal-tDCS will be turned on. The anodal-tDCS stimulation will last for 20 minutes, with an intensity of 2mA, which will be reached after a 30-second wind-up, and it will not be stopped during walking breaks (Fig 2). This stimulation protocol using anodal-tDCS has shown improvements in dual-task gait performance compared to sham stimulation in previous research [45, 46].

#### Group 2: Treadmill + GVRE

Group 2 will follow the same treadmill training protocol as group 1, but will have no anodal-tDCS stimulation.

#### Group 3: Treadmill group

This group will follow the previously explained treadmill gait training protocol with no virtual reality environment nor anodal-tDCS intervention.

### 2.7.- Outcome measures

The main outcome measure will be speed, measured in both the Intermittent Shuttle Walking Test and during Dual Tasking. The rest of gait parameters will be accounted as secondary outcome measures:

Gait parameters during the Intermittent Shuttle Walking Test: Participants will walk along an 8-meter-long zone for 10 round trips at 5 different speeds: preferred, slow, very slow, fast, and very fast (10x5x8m). Based on *Ambrus et al*. [47] this protocol will allow for a lineal relation between stride length and speed to be established with high confidence. During the walk, the following cinematic gait parameters will be recorded via an inertial sensor system APDM® (Opal, APDM, Portland, OR, USA): speed (m/s), stride length (m), gait cycle cadence (Hz), stride length variance coefficient and variance coefficient of the gait cycle cadence.

Gait parameters during Dual Task: Participants will walk along the same aisle as described in the previous variable while carrying out a simultaneous task. Three different types of Dual Task will be assessed: **Mental tracking:** The Mental Tracking Dual Task consists of walking while subtracting 7 serially from 100; **Verbal Fluency**: The Verbal Fluency Dual Task consists of walking while naming words beginning with a specific letter; **Motor Dual Task**: The Motor Dual Task consists of walking while carrying a tray with both hands that has a half-filled glass of water on it. Performance on Mental Tracking Dual Task and Verbal Fluency Dual Task will be assessed in order to evaluate attentional processes during gait [48]. Participants will not be instructed to prioritize the gait nor the DT during the assessment.

To avoid practice or fatigue effects, the Dual Task order will be randomized. Each task will be measured 3 times, resting 1 minute between each try, and using mean data for analysis.

The secondary outcomes and descriptors will include:

Executive function assessment:

In order to assess the participants’ executive functions, two different executive function assessments will be taken via PEBL2 (The Psychology Experiment Building Language), a free software available from http://pebl.sf.net. These executive function tests will measure the response inhibition, reaction time, attention and management of interferences of participants; all related to the GVRE experience. These tests will be the following:

Victoria Stroop Test, which will measure the ability to inhibit cognitive interference [49]. A total of 3 blocks with different words and color stimuli will be assessed, with time taken, responses made and interference as measuring units.Go/No-Go Test, which will measure the participant’s attention and response control [50]. A total of 80 stimuli will be provided, with 20% of those being fake signals that must be ignored. A total accuracy score based on participant responses will be calculated.

Clinical outcomes:

The following scales and tests will be used to assess clinical symptomatology as well as aspects related to quality of life and daily activity autonomy.

Unified Parkinson’s Disease Rating Scale–Part III (UPDRS): UPDRS will be used to assess and monitor PD related disability and impairments. Part 3 of this scale comprises an assessment of different aspects of motor function [51].

Hoehn & Yahr: The assessment using H&Y scale is based on issues of unilateral versus bilateral involvement and the presence or absence of postural reflex impairment [52].

Parkinson’s Disease Questionnaire 39 (PDQ39): This is a patient reported 39-item questionnaire and it assesses PD-specific health related quality of life and disease specific health status [53].

MiniBest Test: This 14-item test is used to assess dynamic balance based on anticipatory postural adjustments, reactive postural control, sensory orientation and dynamic gait [54].

Falls Efficacy Scale International (FES-I): FES-I is a 16-item self-administered questionnaire including a range of functional activities and is designed to assess fear of falling [55].

Montreal Cognitive Assessment (MoCA): MoCA is a 30-question test to assess cognitive function and it evaluates orientation, short-term memory, executive function/visuospatial ability, language abilities, abstraction, animal naming, and clock-drawing test [56].

Any information regarding all the above measurements can be found in http://www.scalesandmeasures.net/. Moreover, a semi structured interview will be added in regards to adherence to treatment, which will allow for a qualitative analysis to explore the experience regarding the GVRE.

Participants will be reminded not to inform the evaluator about their group assignment in order to ensure blinding.

Potential adverse events may include headaches, dizziness and discomfort, due to the GVRE, and skin irritation or redness at the site of tDCS electrode placement during or after the intervention. There may also be issues with training intensity in some cases. However, these risks are considered low and can be minimized through proper screening of participants, monitoring during the intervention, and adequate follow-up.

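### The one named Go/No-Go score pools 64 go and 16 no-go trials, so it cannot separate attention from response control

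*Protocol article*

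**What the plan says.** Section 2.7 of the protocol article (executive function assessment) introduces two computerised tests, the Victoria Stroop and the Go/No-Go, and describes them jointly: "These executive function tests will measure the response inhibition, reaction time, attention and management of interferences of participants". For the second test alone it then states: "Go/No-Go Test, which will measure the participant’s attention and response control". The design of that test follows: "A total of 80 stimuli will be provided, with 20% of those being fake signals that must be ignored". Its scoring is given in one sentence: "A total accuracy score based on participant responses will be calculated".

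No other Go/No-Go score is named. For the Stroop test, the same part of the section lists three measuring units: time, responses and interference. Both tests stand under the line "The secondary outcomes and descriptors will include", so neither is primary. Section 2.8 adds that measurements go onto data sheets, which are shredded once copied into a protected digital file.

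**The concern.** The two kinds of trial test different things. An error on a go trial is an omission, a failure to respond, and bears on attention. An error on a no-go trial is a commission, a failure to withhold a response, and bears on response control. A single total adds the two together with weights set only by the trial counts.

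Executive function is part of the trial's stated aim (end of the Introduction). If the arms differ in total accuracy, the result will not show whether participants attended better or withheld responses better. If the arms do not differ, a gain in one may have been offset by a loss in the other.

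**Working it through.** **Inputs from section 2.7:** 80 stimuli, 20% of them to be ignored, scored as total accuracy. The article gives no derived figure for this test, so there is none to reproduce. It gives no error rates either; those used below are assumptions and are marked as such.

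**Trial counts.** No-go: 0.20 × 80 = 16. Go: 80 − 16 = 64.

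**Score.** Let o be the omission rate on go trials and c the commission rate on no-go trials. Then

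total accuracy = [64(1 − o) + 16(1 − c)] / 80 = 0.8(1 − o) + 0.2(1 − c).

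**What follows from the counts alone:**
- Responding to every stimulus (o = 0, c = 1): 64/80 = 80%.
- Inhibition can move the score by at most 16/80 = 20 points.
- Eight omissions and no commissions: 72/80 = 90%, with a commission rate of 0/16 = 0%.
- No omissions and eight commissions: 72/80 = 90%, with a commission rate of 8/16 = 50%.
- One percentage point of o has 0.8/0.2 = 4 times the effect of one percentage point of c.

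**Offsetting changes (illustrative rates).** If c falls from 40% to 20%, commissions fall from 6.4 to 3.2, a gain of 3.2/80 = 4 points. If o rises from 0% to 5%, omissions rise by 0.05 × 64 = 3.2, a loss of 4 points. Together the total does not move, although the commission rate has halved.

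**Which error type dominates the total?** The omission share of expected errors is 64o / (64o + 16c) = 4o / (4o + c). It exceeds one half only if o > c/4. Under assumed rates:

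| o | c | omission share of errors |
|---|---|---|
| 1% | 50% | 7% |
| 2% | 30% | 21% |
| 5% | 20% | 50% |
| 5% | 10% | 67% |
| 10% | 10% | 80% |
| 20% | 5% | 94% |

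Over assumed ranges of 1% to 20% for o and 5% to 50% for c, the share runs from 7% to 94%. The article does not settle where the trial's participants would fall.

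**Effect of separate scoring.** The participant who responds to everything shows a commission rate of 16/16 = 100% and an omission rate of 0/64 = 0%, instead of a single 80%.

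**The case against.** Attention is one of the two stated constructs, so counting omissions is legitimate and a total that includes them partly fits the purpose. This stands. The fault lies in the pooling, not in the counting of omissions.

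A condensed article may also leave sub-scores of a secondary test to the full protocol or the statistical analysis plan. That would answer a complaint that a score is missing. Here, however, a scoring rule is stated, and the neighbouring test has its measuring units listed. The article does not say that no other Go/No-Go variable will be recorded, so the point is confined to the one score it names.

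The commission rate has its own weakness: a participant who never responds scores 0% commissions. It is also imprecise. At an assumed rate of 30%, one participant's binomial standard error is √(0.3 × 0.7 / 16), or about 11 points. Both remarks are right, and they are why the two rates should be read together.

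Three stronger readings are tempting, and the document does not support them:
- *The total mainly reflects missed go responses.* This is true of the trial weights (64 of 80), but not shown for the errors or for the differences between participants, which depend on rates not given.
- *Reaction time is promised from this test and never scored.* The article assigns reaction time to the two executive tests jointly, not to Go/No-Go.
- *Inhibition is the function that the obstacles and distractors are meant to train.* The article says only that the listed functions relate to the virtual environment. It describes obstacles as prompting changes in walking pattern and distractors as acting on focus.

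**Conclusion.** The point holds in a limited form. The only Go/No-Go score named cannot separate the two constructs that the test is said to measure: complete failure to inhibit still earns 80%, and commission rates of 0% and 50% can both appear as 90%. These results rest only on the stated trial counts and on reading total accuracy as correct responses over all 80 stimuli.

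Whether the pooling would mask or distort a group difference in this trial cannot be said without error rates. Gait speed, the primary outcome, and the sample size are untouched. This is an inexpensive improvement to a secondary outcome.

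**What to change.** In section 2.7, replace the single score with two Go/No-Go outcomes:
- the commission rate on the 16 no-go stimuli, as the measure of response inhibition;
- the omission rate on the 64 go stimuli, as the measure of attention.

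State that the two are interpreted together, so that a general drop in responding is not taken for better inhibition. Keep total accuracy as a descriptive figure. Enter both counts on the data sheet and in the digital file before the sheet is shredded under section 2.8; if only the total is transcribed, the components may be lost.

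The cost is a change of wording and rescoring of responses that a computerised test should already hold, provided trial-level output is kept. The drawback is coarseness: with 16 no-go trials the commission rate moves in steps of 1/16 = 6.25 points.

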### 2.8.- Data collection, management, and dissemination

Demographic data such as age, sex, height, disease duration and most affected side will be collected. Data from outcome measures will be collected at T0, T1 and T2.

In order to maintain confidentiality, all participants will be assigned an identification number through randomization and all data from each participant will be recorded only using the assigned number for each participant. All measurements will be recorded on data sheets. Once the data sheet has been copied to a document in a password protected digital file, the data sheet will be shredded. Other documents to be stored in a locked cabinet include the master list linking the participant’s name to their number as well as contact correspondence. A database validation will be carried out considering the variable range and missing values.

The final trial results will be written into scientific papers and sent to peer reviewed, high quartile journals to disseminate knowledge among the scientific community.

### 2.9.- Statistical analysis

Statistical analysis will be conducted on a blinded intention-to-treat approach. Alfa error will be set at 0.05. The descriptive statistics will use frequencies for the categorical variables and measures of central tendency such as the mean and standard deviation, median and interquartile range for the quantitative variables. Sociodemographic baseline characteristics will be assessed between groups through descriptive statistics. The normality of data distribution and homogeneity of variances will be determined by using the Kolmogorov-Smirnov and Levene’s tests, respectively. The presence of Freezing of Gait will be taken into account as a confounding factor during the analysis process.

Using a mixed methods regression model, data for each variable will be compared between subjects’ factor (Treadmill group, Treadmill + GVRE group, Treadmill + GVRE + anodal-tDCS) and within subjects’ factor on the time points (baseline, post-treatment and a follow-up after 6 weeks of last intervention). Any non-normally distributed data will be log transformed [57]. Multiple imputation by chained equation will be used to manage missing data [58].

Results will be presented as estimated differences with 95% confidence intervals. Gait speed changes will also be expressed in terms of clinically meaningful difference. Based on the study by Hass et al. [36] clinically meaningful differences will be small if the difference is 0.06 m/s, will be moderate if the difference is 0.14 m/s, and will be large if the difference is 0.22 m/s.

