### 2.2.- Sample size

The sample size calculation was based on the study of Mirelman et al [35]. From this study, we assumed that gait speed during a treadmill dual-task assessment in PD patients would be approximately 1.01±0.23 m/s. From the study of *Hass et al*. [36] it was established that an increase of 0.22 m/s in gait speed would be considered clinically relevant. The GRANMO sample size calculator [37] was used to run an analysis of variance calculation.

With an alpha risk of 0.05 and a beta risk of 0.20, assuming a 10% withdrawal rate, and using a two-sided test, it will be necessary to include 26 subjects in each of the three groups.

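### Section 2.9 treats baseline gait speed as one more outcome visit instead of adjusting for it, so the natural treatment contrast is valid but less precise than it could be at no cost

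*Protocol article*

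**What the plan says.** Section 2.9 of the protocol article describes the analysis as follows: "Using a mixed methods regression model, data for each variable will be compared between" the three arms as the between-subjects factor, with a within-subjects factor "on the time points (baseline, post-treatment and a follow-up after 6 weeks of last intervention". Baseline (T0) is therefore one of three modelled outcome levels, alongside post-intervention (T1) and the 6-week follow-up (T2).

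The one adjustment variable named is freezing of gait: "The presence of Freezing of Gait will be taken into account as a confounding factor during the analysis process". Baseline gait speed is not named as a covariate, and nothing is said about holding the arms' baseline means equal. On reporting, the section says: "Results will be presented as estimated differences with 95% confidence intervals". It does not say which difference, though it adds that changes in gait speed will be set against thresholds of 0.06, 0.14 and 0.22 m/s.

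Section 2.1 gives the visits separate roles: T0 describes participants before training, T1 shows the effect of training and how the groups compare, and T2 shows retention. Section 2.2 sizes the trial by an analysis of variance. It assumes that speed "would be approximately 1.01±0.23 m/s" and that "an increase of 0.22 m/s in gait speed would be considered clinically relevant", and arrives at 26 per arm.

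**The concern.** When baseline is a response with its own mean in each arm, the arm-by-visit contrast at T1 equals the difference between arms in raw change from T0 (exactly so with complete data). This subtracts the whole of the baseline value, whereas the best linear use of baseline subtracts only the fraction r of it (equal SDs at both visits). Any r below 1 therefore adds noise, and at r = 0.5 the raw change is no more precise than ignoring baseline altogether.

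The trial plans about 23 evaluable participants per arm, and section 4 reports difficulty in reaching a larger sample. T0 speed is already scheduled for everyone. What is at stake is the width of the confidence intervals and the power for differences smaller than the design effect, including the 0.14 m/s that section 2.9 itself classes as moderate. Validity is not at stake.

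**Working it through.** **Inputs.** SD 0.23 m/s and design difference 0.22 m/s (section 2.2); smaller difference 0.14 m/s (section 2.9); two-sided alpha 0.05, power 80% and 10% withdrawal (section 2.2: "With an alpha risk of 0.05 and a beta risk of 0.20, assuming a 10% withdrawal rate, and using a two-sided test"); 26 per arm. Assumed, because the article gives neither: the correlation r between visits, and an equal SD at each visit.

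**The plan's own figure.** One-way analysis of variance, three groups, largest pairwise difference 0.22, third mean midway. The noncentrality is n × 0.22² / (2 × 0.23²), which is 10.52 at n = 23, and power is 0.817. At n = 22 it is 0.798, so 23 are needed. Then 23 / 0.90 = 25.6, rounded up to 26. The stated sample size reproduces. The calculation uses no baseline information.

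**Variances of a pairwise contrast at T1**, in units of SD² × 2/n:

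- T1 alone: 1
- raw change from T0: 2(1 − r)
- baseline-adjusted: 1 − r²
- ratio of change to adjusted: 2(1 − r) / [(1 − r)(1 + r)] = 2/(1 + r)

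The standard error is 0.23 × √(2 × variance / 23). For example, at r = 0.5 the change contrast has 0.23 × √(2 × 1.00/23) = 0.068 and the adjusted contrast 0.23 × √(2 × 0.75/23) = 0.059.

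**Results.** Power is from the noncentral t with 44 degrees of freedom, two-sided 0.05, with no multiplicity adjustment.

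| r (assumed) | Variance ratio | SE, change | SE, adjusted | Power 0.14, change | Power 0.14, adjusted | Power 0.22, change | Power 0.22, adjusted |
|---|---|---|---|---|---|---|---|
| 0.5 | 1.33 | 0.068 | 0.059 | 52% | 65% | 89% | 96% |
| 0.7 | 1.18 | 0.053 | 0.048 | 74% | 81% | 98% | 99% |
| 0.8 | 1.11 | 0.043 | 0.041 | 89% | 92% | >99% | >99% |

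Outside this range: at r = 0.3 the ratio is 1.54 and the change contrast has about 77% power for 0.22 m/s, against 91% adjusted. At r = 0.9 the ratio is 1.05 and the gain is negligible.

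A simulation of 20,000 trials with a true effect of 0.22 m/s agrees. At r = 0.5 both estimators average 0.220, with standard deviations of 0.068 (change) and 0.059 (adjusted). At r = 0.7 both average 0.220, with 0.053 and 0.049.

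**Conditional case: arm effect averaged over all three visits.** If the arms differ by 0.22 m/s at T1 and T2 and are expected equal at T0, the average is (0 + 0.22 + 0.22)/3 = 0.147 m/s. Under compound symmetry its variance is (1 + 2r)/3 in the same units. Power is about 74%, 66%, 62% and 59% at r = 0.5, 0.7, 0.8 and 0.9.

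**The case against.** The best counter-argument is that a condensed article need not state the tested term, the covariance structure or the baseline handling. A fuller analysis plan may do so, and section 2.9 rules out nothing: a model with T0, T1 and T2 as responses and equal baseline means would fit its description. This is fair as far as silence goes. It does not remove the point, because section 2.9 does set out the layout, places baseline among the outcome levels and names an adjustment variable that is not baseline speed. Read as written, the model does not use baseline efficiently.

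It is also true that a change contrast is valid, that its power for 0.22 m/s is above the planned 80% throughout r = 0.5 to 0.8, and that the trial was not sized for 0.14 m/s. All of that stands and limits the weight of the point.

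A reader might go further and infer that the treatment effect will be the arm main effect, diluted by a third through the baseline visit. The article does not support this. It nowhere says that a visit-averaged arm effect is the test. Crossing arm with time usually points to the interaction, section 2.9 speaks of changes in gait speed, and section 2.1 gives T1 and T2 different purposes. The 0.147 m/s and 59–74% figures are therefore only a reason to exclude that reading explicitly.

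**Conclusion.** The point holds as a free gain in precision. As written, the natural contrast is a difference in raw change from baseline. It is unbiased, but its variance is 33%, 18% or 11% larger than the baseline-adjusted one at r = 0.5, 0.7 or 0.8. The benefit is material for differences near 0.14 m/s if r is about 0.5 to 0.7, and small at 0.8 or above. The design effect of 0.22 m/s is adequately powered by the change contrast unless r is low.

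This rests on an assumed r, equal SDs across visits, 23 evaluable per arm and unadjusted pairwise tests. It is not an error in the sample size, and it does not show that the planned analysis is biased or diluted.

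**What to change.** In section 2.9, state that the mixed model includes arm-by-visit terms and uses baseline in one of two ways:

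- T0, T1 and T2 as responses, with baseline means constrained equal across arms; or
- T1 and T2 as responses, with the T0 value and its interaction with visit as covariates.

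The two are approximately equivalent, and can differ somewhat when data are missing. State also that the treatment effect is the arm contrast at T1, that the contrast at T2 describes retention, and that the arm effect averaged over visits is not used.

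The cost is one or two sentences. T0 speed is already collected, so no participants, visits or measurements are added.

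### The blanket log-transform rule can put gait speed on a ratio scale that has no single reading against the plan's own m/s thresholds, and it does not suit bounded or ordinal scores

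*Protocol article*

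**What the plan says.** Section 2.9 (Statistical analysis) sets up the rule in three steps.

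- Normality is tested first: "The normality of data distribution and homogeneity of variances will be determined by using the Kolmogorov-Smirnov" and Levene's tests. The first test is for normality and Levene's is for the variances.
- One regression model serves all outcomes: "data for each variable will be compared between" the three groups and across the three visits.
- The remedy is "Any non-normally distributed data will be log transformed", with a literature citation. No outcome is exempt, and neither a back-transformation nor an alternative is given.

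The section then fixes the reporting scale: "Results will be presented as estimated differences with 95% confidence intervals", and "Gait speed changes will also be expressed in terms of clinically meaningful difference", with 0.06, 0.14 and 0.22 m/s as the small, moderate and large grades.

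Section 2.2 bases the sample size on a gait speed of 1.01 ± 0.23 m/s and a relevant increase of 0.22 m/s. Section 2.7 makes speed the main outcome, in a shuttle test at five instructed speeds and in three dual tasks. Its secondary measures and descriptors include a Go/No-Go score ("A total accuracy score based on participant responses will be calculated"), the Stroop test ("with time taken, responses made and interference as measuring units"), MoCA, MiniBEST and Hoehn & Yahr.

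**The concern.** The transformation rule and the reporting rule do not fit together. A difference between means of log speed back-transforms to a ratio of geometric means, whereas the thresholds and the sample size are differences in m/s. If speed fails the normality test, following the plan to the letter gives a primary result on a scale that the plan has not said how to read. The scale of the primary result would then depend on a preliminary test of the data, and it could differ between walking conditions that are meant to be compared.

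For secondary measures the question is whether a log can do what the rule asks of it. A log pulls in a long right tail. It stretches a left tail, it cannot turn a variable with two or three values into a normal one, and it does not exist for zero or negative values.

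**Working it through.** **1. The plan's sample size, to see which scale it uses.** Inputs from section 2.2: difference 0.22 m/s, SD 0.23 m/s, two-sided alpha 0.05, power 0.80, 10% withdrawal. A one-way analysis of variance with three groups and assumed means of 0, 0.11 and 0.22 needs 23 per group (power 0.82). Then 23 / 0.90 = 25.6, rounded up to 26, which is the stated figure. The calculation is additive, in m/s.

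**2. The thresholds as ratios.** Ratio = (reference speed + difference) / reference speed. The reference speeds are the plan's mean and mean ± 1 SD: 1.01 − 0.23 = 0.78 and 1.01 + 0.23 = 1.24. Example: (1.01 + 0.14) / 1.01 = 1.139.

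| Reference speed (m/s) | 0.06 m/s as ratio | 0.14 m/s as ratio | 0.22 m/s as ratio |
|---|---|---|---|
| 0.78 | 1.077 | 1.179 | 1.282 |
| 1.01 | 1.059 | 1.139 | 1.218 |
| 1.24 | 1.048 | 1.113 | 1.177 |

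**3. One ratio back in m/s.** Difference = reference speed × (ratio − 1).

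- Ratio 1.139: 0.78 × 0.139 = 0.11; 1.01 × 0.139 = 0.14; 1.24 × 0.139 = 0.17 m/s. The first is below the moderate threshold and the last above it.
- Ratio 1.218 (the design effect): 0.78 × 0.218 = 0.17; 1.01 × 0.218 = 0.22; 1.24 × 0.218 = 0.27 m/s. The first is below the large threshold and the last above it.

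**4. What an unneeded log does to speed.** If speed is truly normal at 1.01 ± 0.23 m/s, simulation gives log speed a skewness of about −0.88. A false alarm would create the asymmetry that the rule is meant to remove.

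**5. Secondary measures.**

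- Scores bounded above. The document gives no distributions, so these shapes are assumed. A MoCA-like score with mean about 24.8 goes from skewness −0.82 to −1.27 after the log. A Go/No-Go accuracy with mean about 0.94 on 80 stimuli goes from −1.24 to −1.47. The direction follows from the concavity of the log; the sizes depend on the assumed shapes.
- Hoehn & Yahr. Section 2.3 admits stages II and III only. With whole stages the baseline has two values, 2 and 3, and their logs are again two values.
- Zero or negative values have no log. The document does not define Stroop interference, so whether it can be zero or negative is not known.

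**The case against.** The strongest reply is that the problem is conditional. Section 2.2 gives no sign that speed is skewed. A Kolmogorov-Smirnov test of the Lilliefors type rejected in about 4% of simulated normal samples of 78, so for normal data the default is an analysis in m/s. This stands: the rule does not put the primary result on a ratio scale, it does so only if a speed variable fails.

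A reader might go further and count eight speed measures at three visits as 24 tests at 5%, giving 1 − 0.95^24 = 71% for at least one false switch. The document does not support that figure. It does not say that normality is tested per visit; one decision per variable gives 1 − 0.95^8 = 34%. Both figures assume independence, although the same participants supply all the speeds. With assumed correlations of 0.7 to 0.9, simulation gave 19–25% for eight tests and 35–54% for 24. An uncorrected Kolmogorov-Smirnov test with estimated mean and SD gave no rejections in 4,000 normal samples. The version is not stated, so no frequency should be quoted.

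A second reply is that grading against the thresholds is announced as an additional presentation and could use raw or back-transformed speeds, and that a ratio can be converted at a chosen reference speed. Both are true, but the plan commits to neither. It is also fair that ± 1 SD describes individuals, and that randomised arm means within one condition will differ far less. The range in the working shows that the grade depends on the reference speed, not how far a trial result would move. Reference speeds should nevertheless differ between conditions, since participants are asked to walk from very slow to very fast.

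A third reply is that such detail belongs in an analysis plan that is not shown, and that the cited source may qualify the rule. Leaving detail out would be no finding. Here the article states a rule without exception and, in the same section, a reporting scale that the rule can break.

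**Conclusion.** The point holds in a limited form: the rule is badly fixed, and the conflict with the plan's own thresholds is contingent. If a gait speed variable is judged non-normal, the log-scale contrast has no single grade: 1.139 reads as 0.11 to 0.17 m/s, and the design effect of 1.218 as 0.17 to 0.27 m/s, over the plan's mean ± 1 SD. Conditions could also end up on different scales. How likely this is cannot be determined from the document.

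For secondary measures, the Hoehn & Yahr point follows from the entry criterion, taking whole stages, although section 2.7 lists outcomes and descriptors together and the scale may serve only as a descriptor. The harm to bounded scores assumes bunching near the ceiling, and the problem of zeros or negatives assumes that such values occur. A reader might infer that the rule is invalid for several named scores; the document gives neither the score distributions nor the interference formula needed to show that.

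**What to change.** In section 2.9, replace the blanket rule with the following.

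- Gait speed is analysed and reported in m/s, untransformed, in every condition and whatever a normality test shows.
- Model residuals are checked, not only the raw data. If they are clearly non-normal, bootstrap or robust-variance confidence intervals for the same mean difference are given as a sensitivity analysis.
- A log is used only for measures named in advance that are strictly positive and right-skewed (Stroop completion time is a candidate), and those results are reported as ratios.
- Bounded and ordinal scores are not logged; an ordinal or rank-based method is used where needed.

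The cost is a few sentences and minor programming, best settled before anyone sees data by arm. The 26 per group stays, because it already rests on a difference in m/s.
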